### Rationale for continuing LIFT_Canada

Earlier in 2019, two large trials presented results, the Enteral Lactoferrin supplementation for very preterm infants (ELFIN trial) [24, 25] and Lactoferrin for Infant Feeding Trial_Australia New Zealand (LIFT_ANZ) [26].

In 2203 infants in the ELFIN Trial (2203 infants), lactoferrin was associated with a relative risk (risk ratio) for late onset sepsis of 0.95 (95% CI 0.86–1.04) [25]. This confidence interval did not reliably exclude a 14% reduction or a 4% increase in sepsis. In the 1417 infants in ELFIN who received formula for > 50% of days of enteral feeds, lactoferrin was associated with a relative risk for sepsis of 0.89 (95% CI 0.79–1.01). This did not reliably exclude a 21% reduction or 1% increase in sepsis in this subgroup. Overall, ELFIN did not rule out important potential benefits, particularly for infants who receive formula for over half of days of enteral feeds.

In 1542 infants in LIFT_ANZ, lactoferrin was associated with a relative risk for late onset sepsis of 0.82 (95% CI 0.63–1.07). LIFT_ ANZ did not rule out a 37% reduction or 7% increase in sepsis. (Presented at the 7th International Conference on Clinical Neonatology, Torino, Italy, May 2019).

When ELFIN is combined with LIFT_ANZ and all other trials, a total of 5011 infants, the overall effect of lactoferrin is to reduce the relative risk of late onset sepsis to 0.82 (95% 0.74–0.92; *P* = 0.0004), with moderate heterogeneity (I^2^ = 0.58) and asymmetric funnel plot, consistent with small study effects (personal communication, [name]).

Similarly, a meta-analysis of the effect of bLF on late onset sepsis in 1891 preterm infants who were not fed exclusively mother’s own milk in two RCTs of bLF supplementation [25, 27, 28], a relative risk of late onset sepsis to be reduced to 0.82 (95% 0.71–0.96; *P* = 0.01), with moderate heterogeneity (I^2^ = 0.64) and asymmetric funnel plot, consistent with small study effects, or true differences between trials in effectiveness or underlying patient risk [29].

This is consistent with a more moderate but clinically relevant average benefit in reducing sepsis with no evidence of harm and no clear increase in mortality, NEC, sepsis or other adverse outcomes. Consequently, a decision to continue enrollment has been supported by the Steering Committee for LIFT_Canada and LIFT_ANZ.

### Aim

Our primary hypothesis is that oral bovine lactoferrin (bLF), through its antimicrobial, antioxidant and anti-inflammatory properties, will reduce the rate of mortality or major morbidity in very low birth weight (VLBW) preterm infants. Thus our aim is two-fold: 1) to test the hypothesis that adding bLF to feeds in preterm babies of less than 1500 g birth weight will (i) improve survival free from major hospital morbidity (primary composite endpoint); and, (ii) have a beneficial effect on each component of the composite primary endpoint, as well as the number of blood transfusions given, length of hospital stay, time to full enteral feeds and growth to 36 weeks corrected gestation (CG); and 2) to evaluate the effect of bLF on survival and developmental outcomes at 24 months corrected age (CA).

## Methods

### Research questions

#### Primary research question

The primary research question: in very low birth weight preterm infants (< 1500 g), does the administration of bLF (200 mg/kg/day) to feeds daily compared to no bLF with feeds daily increase of decrease hospital mortality or major morbidity (defined as brain injury, late onset sepsis (LOS), necrotizing enterocolitis(NEC) at 36 weeks CG or retinopathy of prematurity (ROP) treated before discharge?

#### Secondary research questions

There are several secondary research questions. In very low birth weight infants, does giving bLF (200 mg/kg/day) increase or decrease:
(i)incidence of all-cause in-hospital mortality;(ii)incidence of each of the 5 components of the composite primary outcomes;(iii)chronic lung disease at 36 weeks CG(iv)time to first day of full enteral feeds (≥120 ml/kg/day for 3 consecutive days);(v)number of blood transfusions during the hospital stay;(vi)length of initial hospital stay;(vii)growth at 36 weeks CG as measured by weight and head circumference;(viii)the incidence of death by 24 months CA or the presence of major neurodevelopmental outcomes at 24 months CA, as defined: (i) visual (cannot fixate/ legally blind, or corrected acuity < 6/60 in both eyes), or hearing impairment (requiring a hearing aid or cochlear implants); (ii) cerebral palsy with an inability to walk unassisted; (iii) major developmental delay involving cognition or speech (composite score < 85 for cognition or language on assessment)

### Design

LIFT_Canada is a multi-centre, double-masked, randomized controlled trial with an intention-to-treat analysis. The aim is to enroll 500 infants whose data will be combined with the data of the 1542 infants enrolled from LIFT_ANZ in a pooled analysis (see Fig. 1 for study flow). Eligible infants will be randomized and allocated to one of two treatment groups: 1) a daily dose of 200 mg/kg bLF in breast/donor human milk or formula milk until 34 weeks CG or for a minimum of 2 weeks, whichever is longer, or until discharge home or transfer, if earlier; 2) no bLF with daily feeds.

**Fig. 1 Fig1:**
[figure not shown]
STUDY FLOW CHART

The primary outcome will be determined at 36 weeks CG for the presence of neonatal morbidity and at discharge for survival and treated ROP.

At 24 months CA (with a window of ±6 months, i.e. 18–30 months CA), infants will be assessed with a neurodevelopmental assessment and information related to the status of vision, hearing, and cerebral palsy.

### Randomisation

Upon consent and confirmation of eligibility, the infant will be randomized using a 24-h/day web-based randomization service at the data coordinating centre at the NHMRC Clinical Trials Center in Sydney Australia. A study number will be issued. Study allocation will be randomly allocated in a 1:1 ratio using a minimization approach that stratifies for centre, gender, birth weight (< 1000 vs. ≥1000–1499 g) and according to whether the infant is from a multiple birth.

### Ethics, informed consent, and safety

Documented approval has been obtained from the Research Ethics Board at Sunnybrook Health Sciences Centre which also serves as the Board of Record. Documented approval has been obtained from the Research Ethics Board/Institutional Review Board of all participating centres prior to the start of the study. In addition because bLF is not approved for use in preterm infants, documented approval has been obtained from Health Canada. The study is also designed to conform to the International Conference on Harmonisation, E6: Good Clinical Practice guidelines, and institutional policies.

An interim analysis is planned at 250 infants at which time all adverse events related to the study treatment and any sudden unexpected adverse events reported to Health Canada will be reviewed by the Data Safety Monitoring Committee.

Because the study participants are preterm infants, written informed consent is being obtained from the parents of the infant; infants are not considered for eligibility until a consent has been obtained from one or both parents.

### Eligibility

*Inclusion criteria:*
< 1500 g at birth2–7 days old and not moribundinfant is deemed stable by the clinical care teamhas initiated feeds

*Exclusion criteria:*
severe congenital anomalies which are likely to cause death or known to contribute to an adverse neurodevelopmental outcomemajor congenital gastrointestinal anomalies which will prevent an early approach to feedingparents unable to provide informed consent

### Duration of study period

The daily study treatment will start as soon as possible after randomisation (within 2 days) and continue until 34 weeks CG +/− 5 days or 2 weeks, whichever is longer, or until discharge home or transfer, if earlier.

The study treatment will be discontinued prior to the pre-specified discontinuation criteria if any one of the following occurs:
i.if the infant dies during the study periodii.parental/guardian refusal for ongoing participation with the protocoliii.if the clinical care team determines the need to do so.

If the study treatment is discontinued, participation in the study will continue with the parental/guardian’s permission, and infants will be followed according to the study protocol.

### Study outcomes

#### Primary outcome

The primary outcome is a composite of.

Hospital mortality or major morbidity at 36 weeks CG defined as:
i.Brain injury on ultrasoundii.Necrotizing enterocolitis (Bell stage II or higher)iii.Late onset sepsis (≥ 72 h of life, culture proven), or

Retinopathy of prematurity treated according to local guidelines before discharge from hospital.

#### Secondary outcomes

The secondary outcomes include:
Incidence of all-cause in-hospital mortalitythe incidence of each of the 5 components of the composite primary endpointchronic lung disease at 36 weeks CGTime to first day of full enteral feeds (≥120 ml/kg/day for 3 consecutive days)number of blood transfusionslength of hospital stayweight and head circumference at 36 weeks CGthe incidence of death by 24 months CA or the presence of major neurodevelopmental outcomes at 24 months CA, as defined: (i) visual (cannot fixate/ legally blind, or corrected acuity < 6/60 in both eyes), or hearing impairment (requiring a hearing aid or cochlear implants); (ii) cerebral palsy with an inability to walk unassisted; (iii) major developmental delay involving cognition or speech (composite score < 85 for cognition or language on developmental assessment)

### Statistical analysis

Analysis sets are defined as the following:
The intention-to-treat (ITT) population will comprise all randomized infantsThe Per Protocol population will comprise all randomized infants that receive at least one administration of their assigned treatment and who are not deemed ineligible on blinded clinical reviewA second Per Protocol population will comprise all randomized infants who received the minimum required administrations of 14 days of their assigned treatment and who are not deemed ineligible on blinded clinical review.The safety population will comprise all randomized infants who received at least one dose of the assigned treatment. Infants will be analysed according to the treatment they received for the purposes of the safety analysis.

An interim analysis of the primary composite endpoint and of survival to discharge using the Haybittle-Peto [28] approach in the first 250 infants enrolled in the study in Canada. The procedure involves evaluating the test statistic calculated under the null hypothesis against a boundary of 3 standard deviations (equivalent to χ^2^ = 9, with a *p*-value of 0.0027. This will have a negligible effect on the alpha level applicable at the final analysis.

A two sided alpha (significance level) of 5% will be applied to the analysis of the primary composite endpoint. There will be no adjustment for the interim analysis evaluated using the Haybittle-Peto boundary [30].

The key secondary endpoints for LIFT_Canada comprise the individual components of the primary composite (survival, brain injury, NEC, LOS, and ROP). *P*-values adjusted for the 5 comparisons performed for this set of endpoints will be derived using the Benjami-Hochberg procedure [31] with a family wise error rate of 5%. Results of other endpoints, subgroup, and sensitivity analyses will be interpreted in proper context and with due consideration of type 1 error.

The primary analysis in LIFT_Canada is a pooled analysis utilizing the individual data of infants recruited in Canada combined with the data of the infants recruited in the LIFT_ANZ trial. Safety analyses will be performed using the safety population. Non-safety analyses will be performed using the ITT population. Sensitivity analyses will be performed using the Per Protocol populations. In addition, information will be presented as Canadian data only and combined poled (Canada and ANZ) data.

The primary analysis will be a comparison between treatment groups on the proportion of infants experiencing the primary composite endpoint that is tested using a Wald test (using a χ^2^ distribution) from a log-binomial model fitted using generalized estimating equations to accommodate correlation of data between siblings from multiple births. If the log-binomial model does not converge, a logistic model will be used.

Secondary categorical endpoints will be analysed using the same modelling approach applied to the primary endpoint (i.e. a log-binomial model fitted using the generalized estimating equations to accommodate possible correlation of data between sibling from multiple births; if the log-binomial model does not converge, a logistic model will be used).

A descriptive analysis of adverse events related to the study treatment and those reported to Health Canada in the Canadian cohort will be conducted by treatment allocation. The event rate is expected to be low and an exact test would be the appropriate choice to perform any formal comparisons between the two groups in the proportion experiencing an event related to the study treatment.

Consistency of the treatment effect on the primary endpoint across subgroups will be tested by including a treatment-by-subgroup interaction term (along with the relevant main effect terms) as covariates in the analysis model.

The subgroups of interest are
Birthweight < 1000 g versus 1000-1499 g≤ 28 weeks versus > 28 weeks gestation at birthRandomized ≤72 h versus > 72 h from birthThose who received probiotics by 36 weeks CG (note: this is a post-baseline covariate)Those who received human milk (mother’s own milk or donor human milk) versus formula as initial enteral feeds (note: this is a baseline covariate)

Both human milk as initial feeds and ‘probiotic use by 36 weeks CG are co-variates; an unbiased evaluation of their role as an effect-modifier will be attempted.

Randomisation is stratified by gender, birth weight (< 1000 g vs ≥ 1000-1499 g), single versus multiple birth, and centre. Sensitivity of results obtained from the primary analysis of the primary endpoint to adjustment for stratification factors will be explored by including them as covariates in the model.

Finally, an overall treatment adherence adjusted estimate of the effect of bLF on (i) the primary composite endpoint, and (ii) survival to hospital discharge will be calculated.

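### The second per-protocol set requires 14 days of treatment without exception, so it excludes infants treated as the protocol allows and deaths before 14 treatment days (one sensitivity analysis; low severity)

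*Protocol article*

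**What the plan says.** The Statistical analysis section of the protocol article defines two per-protocol sets. The first takes "all randomized infants that receive at least one administration of their assigned treatment". The second takes "all randomized infants who received the minimum required administrations of 14 days of their assigned treatment". Both then remove infants judged ineligible on blinded clinical review. That review can only take infants out, and no exception to the 14-day condition is stated. Both sets are used for sensitivity analyses; non-safety analyses, including the primary one, use all randomized infants.

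The treatment period appears in two other places. The Design section gives treatment to 34 weeks corrected gestation "or for a minimum of 2 weeks, whichever is longer, or until discharge home or transfer, if earlier". The Duration of study period section repeats this, ending with "whichever is longer, or until discharge home or transfer, if earlier". It also lists reasons for stopping sooner: death, parental refusal, and "if the clinical care team determines the need to do so".

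The Primary outcome section opens its composite with "Hospital mortality or major morbidity at 36 weeks CG defined as" and lists brain injury, NEC and culture-proven late-onset sepsis, together with treated retinopathy.

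**The concern.** A per-protocol set should hold the infants who were handled as the protocol directs. Here the set definition and the treatment rule disagree: fewer than 14 days can be correct under the one and disqualifying under the other.

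The condition is also met or missed after randomization, and one way to miss it is to have a primary event. Infants enter at 2-7 days of age and start treatment within 2 days, so the first 14 treatment days fall in the first weeks of life, when death, NEC and late-onset sepsis already count. A sensitivity analysis that removes part of the endpoint by definition is weak evidence that the primary result is robust. If bLF changes early death or early stopping, which the trial's own hypothesis allows, the two arms lose different infants and the comparison is no longer between randomized groups.

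**Working it through.** The plan states no figure on this point, so there is none to reproduce. The check has two parts.

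**1. The rules side by side**

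- *Discharged home or transferred before 14 days of treatment.* Under Design and Duration of study period, treatment ends as planned ("or until discharge home or transfer, if earlier"). Under the set definition, the infant has not received 14 days and is out. This follows from the text alone.
- *Died before 14 days of treatment.* Death ends treatment, and it is a primary event. The infant is out. This also follows from the text alone.
- *Stopped by the care team after NEC or sepsis.* The stopping clause gives no reason and so covers this case, but does not name it. The 14 days are not said to be consecutive or the first 14, so an infant who resumes dosing can still qualify. Only a permanent stop before 14 days excludes. This part is an inference.

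**2. How far the RR could move (illustration)**

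Inputs from the documents:
- control risk 26% and a 19% relative reduction, i.e. true RR 0.81 and bLF risk 0.26 × 0.81 = 21.06% (Collaboration with LIFT_Australia/New Zealand);
- 500 + 1542 = 2042 infants allocated 1:1, i.e. 1021 per arm.

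Assumptions, because the documents give neither:
- f, the share of infants with a primary event who receive fewer than 14 days;
- g, the share of event-free infants who leave before 14 days.

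Risk within the set = p(1−f) / [p(1−f) + (1−p)(1−g)].

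Example, f = 20% in both arms and g = 0:
- control: 0.26 × 0.8 / (0.208 + 0.74) = 0.208 / 0.948 = 21.9%;
- bLF: 0.2106 × 0.8 / (0.16848 + 0.7894) = 0.16848 / 0.95788 = 17.6%;
- RR = 0.1759 / 0.2194 = 0.802.

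| True RR | f control / f bLF | g | Control risk | bLF risk | RR in set |
|---|---|---|---|---|---|
| 0.81 | 10% / 10% | 0 | 24.0% | 19.4% | 0.806 |
| 0.81 | 20% / 20% | 0 | 21.9% | 17.6% | 0.802 |
| 0.81 | 20% / 20% | 10% | 23.8% | 19.2% | 0.805 |
| 0.81 | 30% / 30% | 10% | 21.5% | 17.2% | 0.801 |
| 0.81 | 10% / 20% | 0 | 24.0% | 17.6% | 0.732 |
| 0.81 | 20% / 10% | 0 | 21.9% | 19.4% | 0.882 |
| 1.00 | 20% / 20% | 0 | 21.9% | 21.9% | 1.000 |
| 1.00 | 20% / 30% | 0 | 21.9% | 19.7% | 0.900 |
| 1.00 | 30% / 20% | 0 | 19.7% | 21.9% | 1.112 |

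With no true effect and losses of 20% and 30%, a two-proportion test at two-sided 5%, ignoring sibling correlation, is significant in favour of the arm with the larger loss about 22% of the time, instead of 2.5%.

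The article's 26% and 19.5% imply RR 0.75 rather than 0.81 (19.5 / 26 = 0.75). The pattern does not depend on which is used: with f = 20% in both arms and g = 0, bLF risk is 0.156 / (0.156 + 0.805) = 16.2% and RR = 0.1623 / 0.2194 = 0.740.

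**The case against.** The strongest reply is that the set decides nothing. The primary analysis is intention-to-treat, the first per-protocol set asks for a single administration, and an adherence-adjusted estimate is already planned for the primary endpoint and for survival to discharge. The article also says that sensitivity results will be read in context. Selection after randomization is a familiar limit of any per-protocol set. All of this stands, and it is why the severity is low.

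A second reply is that a condensed article may leave to the SAP whether an infant discharged or transferred early has met the minimum required. That is possible. But the article itself fixes the number at 14 days and elsewhere ends treatment sooner, so the problem is a contradiction in what is stated, not a missing detail.

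Three stronger readings are tempting and are not supported:

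- *A bias in favour of bLF.* A reader might infer a spurious RR of 0.92-0.88 with no true effect. That follows if 10-15% of events are dropped in the bLF arm only: 0.26 × 0.90 / (1 − 0.026) = 24.0%, ratio 0.924; 0.26 × 0.85 / (1 − 0.039) = 23.0%, ratio 0.884. The trial is described as double-masked, the same 14-day rule applies to both arms, and nothing suggests laxer counting in control. This is a one-arm worst case.
- *Selection on staying event-free.* Removal is certain only for deaths before 14 treatment days. An infant with NEC or sepsis who continues or resumes dosing can qualify.
- *Fourteen days treated as full adherence.* The text calls 14 days a minimum, which is a legitimate exposure threshold for infants due a longer course.

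**Conclusion.** The point holds in a limited form. From the text alone, the second per-protocol set excludes infants whose treatment ended as the protocol provides and removes infants who die before completing 14 days, although death is a primary-endpoint component. Loss of infants with NEC or sepsis is possible but not established.

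Under equal loss between arms the RR hardly moves (0.81 to about 0.80-0.81 for assumed losses of 10-30% of events), although the event rates in the set fall, for example from 26% to 21.9% in control. Under unequal loss of 10 percentage points the RR moves by about 0.07-0.11 in either direction. These sizes rest wholly on assumed shares, so neither the amount nor the direction of bias can be claimed. The primary conclusion is unaffected. Low severity.

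**What to change.** Reconcile the set definition with the Design and Duration of study period sections. For each infant, require the lesser of 14 days and the days due up to death, discharge home or transfer, so that infants who reach one of these while on assigned treatment stay in. Apply the same rule in both arms. This changes only the analysis set, not the treatment rule.

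If the flat 14-day condition is kept, label the analysis a day-14 landmark analysis: infants alive and event-free at day 14 in both arms, later events only. It should then not be presented as a check on the robustness of the intention-to-treat result.

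Infants stopped early by clinical decision would still fall outside the revised set, so the adherence question is better left to the adherence-adjusted estimate already planned.

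The cost is a change of wording, using dosing, death and discharge data that should be on file. The downside is a slightly larger set that includes some infants with short exposure.

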The review showed that lactoferrin supplementation to enteral feeds decreased late-onset sepsis (typical risk ratio (RR) 0.59, 95% confidence interval (CI) 0.40 to 0.87; typical risk difference (RD) -0.06, 95% CI − 0.10 to − 0.02; and NEC stage II or III (typical RR 0.40, 95% CI 0.18 to 0.86; typical RD -0.04, 95% CI − 0.06 to − 0.01. Lactoferrin supplementation did not have an effect on “all-cause mortality” (typical RR 0.65, 95% CI 0.37 to 1.11; typical RD -0.02, 95% CI − 0.05 to 0). Lactoferrin supplementation to enteral feeds with or without probiotics decreased late-onset sepsis involving bacterial and fungal organisms but not chronic lung disease or length of hospital stay. Investigators reported no adverse effects and did not evaluate long-term neurological outcomes and periventricular leukomalacia. However, because of the moderate to low quality of the evidence as per the GRADE criteria [18], the Cochrane review called for the results of at least the 6 additional ongoing trials including LIFT_Canada to provide data to enhance the quality of the evidence.

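### At the single 250-infant look, excess deaths are held to the same two-sided 3 SD boundary as benefit, and a true doubling of mortality would cross it only about 7% of the time

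*Protocol article*

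**What the plan says.** The Statistical analysis section plans "An interim analysis of the primary composite endpoint and of survival to discharge using the Haybittle-Peto" approach, "in the first 250 infants enrolled in the study in Canada". The procedure consists of "evaluating the test statistic calculated under the null hypothesis against a boundary of 3 standard deviations", described as "equivalent to χ^2^ = 9, with a *p*-value of 0.0027". The section adds that the effect on the final alpha is negligible, and it makes no adjustment for the look. The final test of the composite is two-sided at 5% ("A two sided alpha (significance level) of 5% will be applied to the analysis of the primary composite endpoint").

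One boundary serves both endpoints. The article does not use the word symmetric, but a chi-square value has no direction and the stated p-value is the two-sided one. No separate limit for harm is given, and no other look is mentioned. The article does not say what follows a crossing.

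The Ethics, informed consent, and safety section describes a committee review at the same point: "An interim analysis is planned at 250 infants at which time all adverse events related to the study treatment", together with sudden unexpected events reported to Health Canada. It gives no threshold.

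**The concern.** A 3 SD limit is strict so that an early look for benefit uses almost none of the type I error. This is the only justification the article offers, and it does not carry over to harm: acting on excess deaths cannot raise the chance of falsely declaring benefit. Holding harm to 3 SD therefore costs sensitivity without protecting the error rate that the section sets out to protect.

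The sensitivity lost is large because deaths are few in 250 infants. A large true excess would usually leave the boundary uncrossed. Not crossing it could then be taken as reassurance while the remaining 250 Canadian infants (500 planned less 250) are enrolled.

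The adverse-event review at the same look fills the gap only in part. As described, it covers treatment-related events and those reported to Health Canada. Deaths from expected complications of prematurity may not be classed as related to treatment, so an excess of them would show mainly in the all-cause comparison between arms, which is the comparison held to 3 SD.

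**Working it through.** **Inputs**

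- Boundary: 3 SD, chi-square 9, p = 0.0027 (Statistical analysis).
- Size: 250 infants (Statistical analysis). "Study allocation will be randomly allocated in a 1:1 ratio" (Randomisation), so 125 per arm.
- Control mortality: the article gives none for this trial, so it is an assumption. The review cited in the Background reports for all-cause mortality "typical RR 0.65, 95% CI 0.37 to 1.11; typical RD -0.02". If RD = p × (RR − 1), then p = 0.02 / (1 − 0.65) = 0.02 / 0.35 = 5.7%. Rounding of the RD (0.015 to 0.025) gives 4.3% to 7.1%. This is approximate, because a pooled RR and a pooled RD need not correspond exactly. A wider range of 4% to 10% is also shown.

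**Step 1: reproduce the stated p-value.** 2 × (1 − Φ(3)) = 0.00270, which equals P(chi-square on 1 df > 9). The one-sided value would be 0.00135. The stated 0.0027 is therefore correct and two-sided.

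**Step 2: the alpha statement.** With a final two-sided critical value of 1.96 and one earlier look at 3 SD, the overall alpha is 0.051 at information fraction 250/500 and 0.052 at 250/2042. The statement that the look has a negligible effect is not in dispute.

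**Step 3: deaths needed to cross.** Take Z = (d₁ − d₀)/125 ÷ √[p̄(1 − p̄) × 2/125], where d₁ and d₀ are deaths on bLF and control and p̄ = (d₁ + d₀)/250.

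Example with 8 control and 24 bLF deaths: p̄ = 32/250 = 0.128; SE = √(0.128 × 0.872 × 0.016) = 0.0423; difference = 16/125 = 0.128; Z = 3.03. With 23 bLF deaths Z = 2.88, which does not cross.

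| Control deaths | bLF deaths needed for 3 SD | Ratio |
|---|---|---|
| 5 | 19 | 3.8 |
| 8 | 24 | 3.0 |
| 10 | 27 | 2.7 |
| 12 | 30 | 2.5 |

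**Step 4: chance of crossing in the harmful direction if mortality truly doubles.** Exact enumeration of two independent binomials with 125 per arm, summing the probability of all pairs with Z ≥ 3 or Z ≥ 2. The last column uses equal rates in both arms.

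| Control mortality | 3 SD, doubling | 2 SD, doubling | 2 SD, no effect |
|---|---|---|---|
| 4% | 3.3% | 24% | 2.0% |
| 5.7% | 7.1% | 35% | 2.0% |
| 6% | 7.9% | 37% | 2.1% |
| 8% | 13.8% | 49% | 2.2% |
| 10% | 20.9% | 60% | 2.3% |

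Over the rounding range 4.3% to 7.1%, the 3 SD figure runs from 4% to 11%.

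**Step 5: robustness.**

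- A true tripling at 5.7% crosses 3 SD 44% of the time.
- The chance of crossing under a doubling reaches 50% only when control mortality is about 16.5%. That would be well over half of the 26% control rate given for the whole composite.
- A Wald statistic on the log relative risk, the type planned for the final analysis, is less sensitive: 2.1% at 5.7% and 15.5% at 10%.
- Correlation between siblings, and infants not yet discharged at the look, would lower the figures further.

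**The case against.** **The text may be only part of the rule.** This is a journal article, and a harm guideline often sits in the full protocol or the committee's charter. This stands in part. The silence of the article does not show that the trial lacks such a guideline. But the article does not merely omit a rule: it states one for survival to discharge and gives its rationale, and that rule can be assessed as written.

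**The committee can act on judgement.** This stands. A reader might infer that the committee is barred from acting on excess deaths below 3 SD, or that it would receive no warning of them. The documents do not support this. They do not say that a crossing is required before the committee acts, nor what a crossing leads to, and the committee reviews safety data at the same look.

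**A doubling is unlikely.** This stands as a limit on urgency. The cited review's interval for the mortality relative risk is 0.37 to 1.11, and the section on the rationale for continuing, written after two large trials, reports no clear increase in mortality. It lowers the prior probability of harm, but gives no reason for the harm side to need the same evidence as benefit.

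**A two-sided boundary suits a two-sided question.** The research questions ask about increase or decrease, so the choice is coherent. Nothing is misstated; the point is that the stated reason covers one direction only.

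**A 2 SD guideline also misses most doublings.** This stands at control rates up to about 8%. At 5.7%, a doubling means about 7 deaths against 14, for which Z is only 1.6. The small number of deaths is the main limit, and no threshold at this look removes it.

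**The same could be asked for necrotizing enterocolitis.** No calculation here supports a boundary for it, so none is proposed.

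**Conclusion.** The point holds as a worthwhile improvement, not as an error. The article applies one direction-blind 3 SD boundary to survival to discharge at its only stated look, on a rationale that concerns benefit alone. A true doubling of mortality would cross it about 7% of the time at 5.7% control mortality, and 3% to 21% of the time over 4% to 10%.

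This rests on 125 infants per arm with known outcome, independent infants, a pooled-variance test, and a control mortality that is not stated for this trial. The conclusion that a doubling would usually not cross fails only above about 16.5% control mortality.

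It does not follow that the trial is unsafe or that the committee's hands are tied. What follows is narrower: with this boundary, not crossing says little about mortality.

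**What to change.** Keep 3 SD for benefit. Add one sentence to the protocol and the monitoring charter setting a separate, non-binding, less extreme guideline for excess all-cause in-hospital mortality at the same look, for example 2 SD in the harmful direction. Reaching it would prompt the committee to review all unmasked data together with the LIFT_ANZ and external evidence and to make a recommendation; it would not stop the trial automatically. State also that not crossing the guideline is not evidence of safety. If the charter already holds such a guideline, cite it and the point is closed.

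The gain is a rise in the chance of flagging a true doubling from about 7% to about 35% at 5.7% control mortality (from 3%–21% to 24%–60% over 4% to 10%). The cost is about a 2% chance of an unneeded review if there is no effect, and a small loss of power if a false alarm led to stopping. It needs no extra infants and spends no alpha for benefit.
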